#### 2.3.2. Phase 2: Cluster-Randomized Clinical Trial Across Different Primary Care Centers in Countryside of Tarragona, Spain

A cluster-randomized clinical trial will be carried out for 12 months. The study will be conducted in 20 primary care centers in the Tarragona area. These centers will be randomly allocated into two groups at a ratio of 1:1. The intervention group will have the home care visual map available. No blinding will be implemented in this study. This open-label design is chosen due to the nature of the interventions, which will make blinding unfeasible

This phase of this study will follow the SPIRIT Statement guidelines for reporting clinical trial protocols.

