##### Sample Size

The expected effect size is a 10% reduction in hospital admissions, based on the baseline hospital admission rate of 65.89% in 2024 for the home care program at primary care centers in Tarragona, which belong to the Catalan Health Institute. We assumed a 95% confidence level (alpha error of 5%) and a statistical power of 80%. Additionally, a 15% loss to follow-up was factored into the calculation. With these assumptions, a total of 272 patients per group (control and intervention) will be required. The ARCSINUS approximation (GRANMO Sample Size Calculator v.8.0, available at www.datarus.eu/aplicaciones/granmo/) was used.

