##### Variables

The main outcome variables of this study are as follows:The proportion of patients with hospital admissions and avoidable hospital emergency visits (main variable) during the follow-up period.The percentage of patients with ulcers and falls.The total number of avoidable admissions and hospital emergency visits during the follow-up period.The total number of deaths and definitive institutionalizations.Quality of life, measured using the EuroQol-5D index, a record currently available in EMRs [22].

The following are considered as covariates:Age, sex, and socio-economic level [23] and the home care model.Main comorbidities, following the Charlson comorbidity index [24].

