##### Data Analysis

Continuum variables will be described using means and standard deviations if they follow a normal distribution or using means and interquartile ranges otherwise. The normality of the variables will be described using the Kolmogorov test. Categorical variables will be described with percentages and 95% confidence intervals.

Outcomes will be compared between groups using the Chi-square test. A multivariate analysis (Cox regression) will be performed, introducing adjustment variables into the model: socio-demographic variables, risk areas, and covariates, as mentioned before. Covariate selection will be based on clinical relevance and statistical significance (*p* < 0.05 in univariate analysis or established predictors from previous research). The time until the event of the main outcome variables will be considered in the model.

For the “quality of life” outcome, the test scores (averages and percentiles) will be compared between the control and intervention groups at the beginning and at the end of the intervention using the *t* test.

Missing data will be handled under the principle of the worst-case scenario. However, different imputation strategies may be considered depending on the context.

The statistical package R (R foundation for statistical computing, Vienna, Austria; version 4.1.2 or later) will be used for all analyses. Statistical significance shall be established at *p* < 0.05.

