The visual map will enable healthcare professionals to determine appropriate actions based on the color-coded health areas, whether by implementing health promotion activities, undertaking preventive measures, or addressing existing issues requiring intensive intervention. Moreover, having a standardized visual map for all healthcare professionals will ensure continuity in care and enhance the monitoring of home care patient performance [34].

Despite its advantages, the visual map will have some limitations, including potential technological complexities in implementing EMRs. These challenges may involve integration with existing systems, data accuracy, and the adaptation of the tool to the specific needs of various healthcare settings. Moreover, organizational barriers, such as workflow disruptions and resistance from healthcare professionals, may also affect the tool’s adoption. However, the research team has extensive experience in innovation and the implementation of various technological tools in the field of quality and patient safety [35,36]. In fact, some of these innovations have been successfully scaled up and integrated across the entire autonomous community. To further support the implementation of the visual map, a training session will be conducted at the start of this study, and monthly meetings will be held to monitor usage, address concerns, and provide ongoing support to professionals. This experience and structured support plan will help mitigate the challenges and facilitate the smooth adoption of the tool.

In phase 2 of this study, different socio-demographic and socio-economic characteristics of the patients enrolled could influence the results. To mitigate these differences, similar centers will be selected and a comparative descriptive baseline analysis between the control and intervention groups will be conducted. This approach will help reduce potential bias and improve the robustness of the findings.

Incorporating phase 3 in this study will be crucial for gathering qualitative user feedback on the visual map to ensure that it fits well within the work environment and is intuitive to use. This adaptation aims to increase the use of the visual map in daily routines, ultimately leading to time savings for HCNs [37].

In conclusion, the visual map will enhance the safety of vulnerable patients in a less controllable environment, promoting patient safety, and aiding in resource management and distribution decision-making.

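### The EuroQol-5D comparison at the end of the trial ignores the baseline score already collected, losing precision and carrying over part of any chance baseline imbalance

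*Protocol article*

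**What the plan says.** The Variables section lists among the main outcomes "Quality of life, measured using the EuroQol-5D index, a record currently available in EMRs". The Data Analysis section gives this outcome its own sentence: average and percentile scores "will be compared between the control and intervention groups at the beginning and at the end of the intervention", by t test. On a plain reading these are two cross-sectional between-arm tests. The sentence names no change score, baseline covariate or regression model.

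The only adjusted analysis in the section is for events: "A multivariate analysis (Cox regression) will be performed, introducing adjustment variables into the model". A Cox model cannot analyse a EuroQol score. The listed covariates are "Age, sex, and socio-economic level [23] and the home care model", plus the Charlson index; baseline EuroQol-5D is not among them.

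On baseline differences, the Discussion says that "similar centers will be selected and a comparative descriptive baseline analysis between the control and intervention groups will be conducted". Allocation is by centre, with 20 centres: "These centers will be randomly allocated into two groups at a ratio of 1:1".

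**The concern.** The plan measures the same score at both ends of follow-up but analyses the end score as if the first did not exist. Part of the spread in end scores is stable difference between patients, which the baseline score would explain. Leaving it in the residual widens the confidence interval for the effect on quality of life.

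A second cost follows from the number of centres. With about 10 per arm, the arms can differ at baseline by chance. An unadjusted end comparison keeps the part of that difference that persists. Testing the baseline difference, or describing it, does not remove it from the end result.

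At stake is the precision and credibility of one of the main outcomes. The primary outcome is not affected.

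**Working it through.** **Is there a plan figure to reproduce?** No. The article gives no SD, target difference, correlation or ICC for EuroQol-5D. Its sample size is built on admissions only ("The expected effect size is a 10% reduction in hospital admissions, based on the baseline hospital admission rate of 65.89% in 2024"), so 272 per group serves here only as a count of patients.

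**Inputs from the article:** 20 centres at 1:1, so 10 per arm if split equally; 272 patients per group, so 272/10 = 27.2 per centre; 15% loss, so 272 × 0.85 = 231 completers per group; alpha 5% (taken as two-sided) and power 80%.

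**Assumptions:** rho from 0.3 to 0.7; ICC from 0 to 0.10; equal SDs at both times.

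**Step 1: patient-level variance.** Adjusting for baseline multiplies the residual variance by 1 − rho², so the saving is rho².

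| rho | saved | left |
|---|---|---|
| 0.3 | 9% | 91% |
| 0.5 | 25% | 75% |
| 0.6 | 36% | 64% |
| 0.7 | 49% | 51% |

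**Step 2: detectable difference, ignoring clustering.** (1.96 + 0.84) × √(2/231) = 0.261 SD for the end-only t test. Multiplying by √(1 − rho²) gives 0.249, 0.226, 0.209 and 0.186 SD for rho of 0.3, 0.5, 0.6 and 0.7. These figures are optimistic for a cluster trial.

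**Step 3: the gain under clustering.** The variance of the arm difference is proportional to ICC + (1 − ICC)/m, with m = 27.2. If adjustment shrinks only the patient-level part, the saving is rho² times that part's share.

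- ICC 0.05: 0.95/27.2 = 0.0349; share 0.0349/(0.05 + 0.0349) = 0.411. Saving: 0.25 × 0.411 = 10% (rho 0.5); 0.49 × 0.411 = 20% (rho 0.7).
- ICC 0.02: 0.98/27.2 = 0.0360; share 0.0360/(0.02 + 0.0360) = 0.643. Saving: 0.25 × 0.643 = 16% (rho 0.5); 0.49 × 0.643 = 32% (rho 0.7).

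At rho 0.3 the savings are 0.09 × 0.411 = 4% and 0.09 × 0.643 = 6%. If baseline also explains differences between centres, the saving is larger than these figures.

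**Step 4: chance imbalance and carry-over.** The SE of the baseline arm difference in SD units is √(2 × DE/272), where the design effect DE = 1 + (27.2 − 1) × ICC. The 95% chance range is ±1.96 SE.

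| ICC | DE | SE | 95% range |
|---|---|---|---|
| 0 | 1.00 | 0.086 | ±0.17 SD |
| 0.02 | 1.52 | 0.106 | ±0.21 SD |
| 0.05 | 2.31 | 0.130 | ±0.25 SD |
| 0.10 | 3.62 | 0.163 | ±0.32 SD |

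The expected carry-over into the end difference is rho times the imbalance, taking rho to hold at centre level too. At ICC 0.05 and the edge of the range, that is 0.5 × 0.255 = 0.13 SD or 0.7 × 0.255 = 0.18 SD.

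**Step 5: would a change score do as well?** Its variance relative to the end-only test is 2(1 − rho): 1.40 at rho 0.3, 1.00 at 0.5 and 0.60 at 0.7. It helps only above rho 0.5, and at 0.7 it still leaves more variance than adjustment does (0.60 against 0.51).

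**The case against.** The strongest reply is that the planned comparison is valid. Centres are randomised, so the end comparison is unbiased on average, and it is itself a between-arm test of the intervention. That stands. A reader might infer that the result is confounded by any baseline difference. The document does not support this: the issue is chance imbalance in a given allocation, and only about a share rho of it persists.

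A reader might also infer that a non-significant test at the start and a significant one at the end will be taken together as proof of effect. The article nowhere says so.

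The size is open to challenge too. Rho and the ICC are not in the document, the gain is nil at rho 0, and a patient-level saving overstates the gain in a cluster trial. All of that is right, which is why step 3 gives the smaller figures.

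Finally, the article is condensed. Its Expected Results section promises to report how health outcomes change over the year, and the Discussion plans to choose similar centres. Choosing similar centres may reduce imbalance. But neither statement puts the baseline score into the end comparison, and the Data Analysis section does not leave the method open: it names the t test. This is a stated choice that can be improved, not a detail left to an analysis plan.

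**Conclusion.** The point holds as one of efficiency and of robustness to chance imbalance, not of bias. The end-only t test discards baseline information that the trial collects, and the baseline test repairs nothing. With about 27 patients per centre, and if only patient-level variance shrinks, adjustment would lower the variance of the arm difference by about 10% to 20% (rho 0.5 to 0.7) at an ICC of 0.05 and by about 16% to 32% at 0.02. The corresponding patient-level figures, 25% to 49%, should not be read as the gain for the trial. Rho and the ICC are assumptions. That the plan makes no adjustment is clear from its wording; how much this costs is not. Quality of life is a listed main outcome but not the one marked as the main variable, so the main conclusion is untouched.

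**What to change.** Replace the two t tests with one linear mixed model of the end-of-study EuroQol-5D index on arm and baseline index. Include a random centre effect, because centres are the unit of randomisation, and a small-sample degrees-of-freedom correction (Kenward-Roger or Satterthwaite), because there are only 20 of them. Report the adjusted mean difference with its 95% confidence interval. Describe baseline scores by arm without a significance test.

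The cost is a change of wording in the Data Analysis section. The plan already compares baseline scores, so no extra data, visits or patients are needed.

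### The only named missing-data rule is an undefined worst case with an open-ended alternative; depending on how it is read, it could shrink, shift or reverse the difference in admissions

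*Protocol article*

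**What the plan says.** The Data Analysis section for Phase 2 names one rule, without restricting it to any outcome: "Missing data will be handled under the principle of the worst-case scenario". It does not say what value stands for the worst case, or whether both arms are coded alike. The following sentence adds that "different imputation strategies may be considered depending on the context", without naming a method, a trigger or a decision point.

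The same section compares outcomes by chi-square test, fits a Cox regression that uses time to the main outcome events, and compares quality of life by t test. The main variable (Variables section) is a proportion of patients with admissions and avoidable emergency visits. The introduction to Phase 2 describes an unblinded trial with centers allocated 1:1.

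The Sample Size section states that "a 15% loss to follow-up was factored into the calculation". The section on data collection says that most data come from the electronic medical record (EMR), but does not list admissions among the examples.

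**The concern.** A worst-case rule is often thought conservative. As a main rule for a binary outcome it is conservative only under some codings and some patterns of loss. Counting missing as an event in both arms pulls the arms together when loss is equal, and creates a difference when it is not. Coding the arms in opposite directions penalizes the intervention by the full amount of missing data. The text does not say which is meant.

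Nor does the rule carry over to the other planned analyses. An imputed admission has no date, which the Cox model needs, and the worst case has no stated meaning for a EuroQol-5D score. Because alternatives are left open without a criterion, the plan does not rule out choosing the method after unblinded results are known. At stake are the size, and under one reading the sign, of the main estimate.

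**Working it through.** **Inputs (Sample Size section).** Control risk p1 = 0.6589 ("based on the baseline hospital admission rate of 65.89% in 2024"); "The expected effect size is a 10% reduction in hospital admissions"; 15% loss; 272 per group; alpha 5%; power 80%; arcsine approximation. Assumptions: the 10% is absolute, so p2 = 0.5589; the test is two-sided; patients with missing outcomes have the same admission risk as the others in their arm; clustering is ignored, so the power and rejection figures are optimistic for this design.

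**The plan's own figure.** With h = 2·asin√p1 − 2·asin√p2 = 0.2053, n = 2·((1.960 + 0.842)/h)² = 372 per group, or 438 after dividing by 0.85. One-sided gives 293, or 345 after loss. A relative 10% reduction gives 845, or 994 after loss. None gives 272. That is a separate matter; 272 is used below only as the planned number.

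**Reading A: missing = admission in both arms, equal loss m.** Each risk becomes q = p(1 − m) + m, so the difference is (p1 − p2)(1 − m).

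- m = 5%: 10.0 × 0.95 = 9.5 points.
- m = 10%: 10.0 × 0.90 = 9.0 points.
- m = 15%: 0.6589 × 0.85 + 0.15 = 71.0% versus 0.5589 × 0.85 + 0.15 = 62.5%, or 8.5 points.
- Relative reading of the effect, m = 15%: 6.6 × 0.85 = 5.6 points.

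Power at 272 per group with m = 15% is 55.9%. Analyzing only the 272 × 0.85 = 231 observed per group gives 59.8%, and complete data give 66.8%. The rule itself therefore costs about 4 points of power against observed cases.

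**Reading A, unequal loss, no true effect.** The false difference is (1 − p1) × (difference in loss) = 0.3411 × (difference in loss). The document gives no loss by arm, so these splits are assumptions that average 15%:

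| Loss, control / intervention | False difference | Rejection at nominal 5% |
|---|---|---|
| 15% / 15% | 0 points | 5.0% |
| 12.5% / 17.5% | 1.7 points | 7.2% |
| 10% / 20% | 3.4 points | 14.1% |

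More loss under intervention looks like harm; more loss under control looks like benefit. With a true 10-point effect, 10%/20% leaves 4.6 points and 20%/10% inflates it to 12.4.

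**Reading B: missing = admission under intervention, no admission under control, equal loss m.** The apparent benefit is (p1 − p2)(1 − m) − m.

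- m = 5%: 9.5 − 5.0 = 4.5 points.
- m = 15%: 0.6589 × 0.85 = 56.0% versus 62.5%, an apparent harm of 6.5 points.
- The sign changes at m = 0.10/1.10 = 9.1%.

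**Cox model.** The outcome there is a time. Neither reading supplies a date for an imputed event, and the section gives none.

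**The case against.** Several stronger statements are tempting and are not supported.

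- *That the protocol assigns an admission to every lost patient.* It does not; this is one reading of an undefined rule. An article may leave detailed coding to a fuller document that is not shown. What stands is that the article itself states a rule and then reopens it.
- *That 15% of main outcomes will be missing.* The 15% is a sample-size allowance. With most data coming from the EMR, missing admissions could lie anywhere from near 0 to 15%, and the largest figures above belong to the top of that range.
- *That all imputed events would be invented.* At the plan's own control risk, about two thirds of lost controls would have been admitted anyway. Under Reading A at 15%, falsely added events are 0.15 × 0.3411 = 5.1 of 71.0 points in control (about 7%) and 0.15 × 0.4411 = 6.6 of 62.5 in intervention (about 11%).
- *That the rule explains the low power.* Most of the gap from 80% arises because 272 does not follow from the stated inputs.
- *That loss will differ between arms.* Nothing in the document predicts it. It is plausible in an open-label trial run through the allocated centers, but the splits are assumed.
- *That the rule contradicts the Cox model or the sample-size calculation.* The text does not say how lost patients enter the Cox model, and since 272 cannot be reproduced, how loss was allowed for cannot be seen. These are gaps, not documented contradictions.
- *That the open clause is meant for choosing after sight of the data.* It may mean that different outcome types need different methods. It neither says so nor excludes a late choice.

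Censoring at last contact is not assumption-free either, in a frail population where death and institutionalization are themselves outcomes. Multilevel imputation is one acceptable choice among several.

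**Conclusion.** The point holds in conditional form. The protocol article makes an undefined worst case its only named rule for missing data and leaves alternatives open without criterion or timing, in an unblinded trial. This is a defect in what is stated, not merely absent detail.

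The numerical effect depends on the reading and on how much is missing. Coding missing as an event in both arms removes at most 1.5 of 10 points, at a small cost in power. Differential loss adds about 0.34 points per point of imbalance, in either direction, so the rule is not reliably conservative. Opposite coding by arm would reverse a true 10-point benefit once more than about 9% of outcomes are missing, so the two readings can lead to opposite conclusions. Confidence is high for the vagueness and the formulas; the amounts of bias rest on assumed missingness. The change should be made, but the document does not show that the primary result will be biased.

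**What to change.** 1. Take admissions and deaths from the EMR or hospital record for every consented patient, including those who stop visits, so that the main variable is rarely missing.
2. Prespecify the primary analysis on all observed data, allowing for clustering by center, with censoring at last contact in the Cox model.
3. Name one method for EuroQol-5D and covariates, such as multilevel multiple imputation.
4. Keep the worst case as a sensitivity analysis, with its coding written out for each outcome and each arm.
5. Delete the clause "different imputation strategies may be considered depending on the context".

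The cost is protocol or SAP wording and modest programming, since records are already the main data source. The price is that the primary analysis then assumes non-informative loss; the defined worst-case analysis shows how far the conclusion depends on that.

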#### 2.3.3. Phase 3: Qualitative Study

##### Design

A qualitative study through semi-structured interviews and focus groups will be performed. The objective of this phase will be to assess the impact of the use of the home care visual map on the healthcare professionals who attend home care patients. This study will assess the usability and effectiveness perceived by the healthcare professionals (whether it facilitates the identification of patient problems, prioritization, and decision-making in healthcare practice and if it is valued as a beneficial tool).

##### Participants

The selection process of the participating healthcare professionals will be carried out based on the specific parameters of this study and aim at finding the maximum variability, heterogeneity, and significance with similar representation by the collective group (medicine, nursing, social work), place of work (rural, urban), and home care model (home care team or basic units). A flexible sampling design will be conceived that also accommodates a circular view of this research and where reformulations can take place based on the results that are obtained throughout the fieldwork.

##### Data Collection and Resources

Data collection will be performed through conversational or narrative techniques, although observation and documentary analysis will also be used.

For the conversational or narrative techniques, the research team will realize semi-structured interviews and focus groups (both with a thematic script) that will allow the collection of information and contextualization, as well as the triangulation of information.

To assess the impact of the visual map implementation in improving the healthcare practice of healthcare professionals, the professional risk category (nurse, social health worker, and physician) and years of experience in primary care will be taken into account.

